**Fig. 1 Fig1:**
[figure not shown]
Standard Protocol Items: Recommendations for Interventional Trials (SPIRIT) Figure of stepped-wedge study design, illustrating stepped roll-out of the intervention, enrolment and data collection activities over time

We chose a stepped-wedge design as the most efficient and pragmatic trial design for our purposes, using methodology described by Hemming et al. [32–34]. Stepped-wedge designs can be useful for investigating the effects of an intervention that is likely to be beneficial in real-world environments. For this reason, it has been used increasingly for evaluating service delivery type interventions in developing countries, and is regarded as a pragmatic design suited to real-world settings [32]. We wanted all hospitals to receive the intervention and we had preliminary data suggesting that it was an effective intervention. We wanted to roll the intervention out sequentially, so it was not feasible to do parallel randomisation. We anticipated moderate intra-cluster correlation meaning that the stepped-wedge design would be relatively efficient. The pulse oximetry provision and training will be done before the full intervention as a ‘phase I’, as hypoxaemia data is necessary for evaluation of the full intervention.

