### Intervention

The intervention will involve the implementation of a comprehensive oxygen delivery system in the children’s and neonatal wards of 12 secondary-level hospitals in southwest Nigeria.

We used a participatory planning approach to develop the intervention and plan implementation. This involved the coordination team visiting all potential sites, conducting a mixed-methods needs assessment [8], bringing key stakeholders from each hospital together for a planning workshop, and meeting with state health authorities. Following this, the general design and components of the intervention were reviewed by revisiting the programme theory derived from past experience, results of the needs assessment, and feedback from healthcare workers, technicians, and administrators at participating hospitals. We based the intervention design on a theory-based analysis of previous oxygen projects, and used quality improvement principles, evidence-based teaching methods, and behaviour-change strategies.

Phase I involves the introduction of pulse oximeters to all participating hospitals, and the commencement of prospective data collection. The early introduction of pulse oximetry will enable accurate classification of severity of illness and indication for oxygen (which is needed for primary analysis) and will give all hospitals a tangible sign of involvement even while they are waiting for full oxygen system installation and training. During phase I, each participating hospital will be visited by the coordination team at least once to work out the site-specific approach to implementing the comprehensive oxygen system (phase II).

Phase II involves the introduction of the comprehensive oxygen system, including (1) standardised oxygen equipment package, (2) clinical education and support, (3) technical training and support, (4) procurement, installation and maintenance structures, (5) infrastructure support (including improved electricity supply using solar technology where needed), (6) strengthening disease surveillance and health information systems, and (7) strengthening quality improvement processes. This is described in detail in Table 3.

**Table 3 Tab3:** ‘Improved oxygen system’ intervention components, purpose, and description

Intervention component	Purpose(s)	Description

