Standardised equipment package oxygen concentrator pulse oximeter oxygen delivery equipment maintenance gear	To enable reliable, continuous access to oxygen for all children and neonates To make it easy to use oxygen correctly To make it easy to maintain oxygen equipment in good function	Selection of quality, user-friendly equipment that is proven to function in hot, humid environments and capable of being maintained with minimal technical skill: Airsep Newlife Elite oxygen concentrator, Lifebox pulse oximeter (neonatal and child probes), Airsep Sureflow flowmeter assembly, nasal prongs and tubing, oxygen analyser, installation and maintenance gear
Clinical education and support basic oximetry training healthcare worker training on the clinical use of oxygen supportive supervision	To build healthcare worker capacity and motivation to use oxygen well To stimulate healthcare workers to make their work environment more conducive to good clinical care	Clinical training material based on WHO guidelines [35, 48] and will include: clinical approaches to sick children; recognition and treatment of hypoxia; use of pulse oximetry and concentrators. Using Merrill’s approach to active learning [31], training will be active, task-based, and intentionally target motivation. Training conducted on-site at participating hospitals. One-hour basic pulse oximetry training for nurses and physicians when pulse oximeters are distributed. Half-day training on the clinical use of oxygen at the time of installation, using an ‘apprentice’ model where individual leaders are trained first, and then they are supervised to train their colleagues (and coordinate future re-training)
Technical training and support technician training on maintenance and repair supportive supervision	To build technician capacity and motivation to maintain and repair equipment To stimulate technicians to modify their procedures to make equipment care easier	Technical training material adapted from previous projects [12, 14, 15] and delivered by an expert biomedical engineer. Three-day training conducted at a central location for central engineers and at least one technician from each participating hospital. Regular supervision visits (at least 3 monthly) for re-training, review and feedback, and to identify areas needing additional attention

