### Outcome measures

To achieve our primary objective of understanding how to most effectively implement oxygen systems, our mixed-methods evaluation will assess effectiveness, process and fidelity and measure a range of clinical, quality of care, technical, and health systems outcomes (including cost, sustainability, and managerial/policy implications) (Table 4).

**Table 4 Tab4:** Outcome measures used to evaluate the Nigeria Oxygen Implementation Project with associated research question and data source

Category	Research question(s)	Outcome measures	Data source
Clinical effectiveness	Does the intervention improve outcomes for the target population (specifically child pneumonia, pre-term/small neonates)?	Under-five case fatality rate (all-cause) Under-five pneumonia case fatality rate Neonatal case fatality rate Pre-term/small neonatal case fatality rate	Case notes
Epidemiological	What are the characteristics of patients with hypoxaemia in these hospitals?	Mean duration of hypoxaemia, oxygen therapy Descriptive statistics regarding hypoxaemia and oxygen therapy (age, condition, illness severity, etc.)	Case notes
Quality of care – oxygen practices	Can healthcare works correctly identify, treat, and monitor children and neonates who need oxygen therapy? Does the intervention improve healthcare workers’ oxygen care practices? How is the intervention adopted by healthcare workers? What training and supervisions is required to change practice?	Proportion of hypoxaemic children who correctly received oxygen therapy Proportion of admitted children who have pulse oximetry done correctly during admission Proportion of children receiving oxygen who had a documented clinical indication for oxygen Mean quality of care score for oxygen therapy Mean knowledge/skill scores Attitudes, behaviours, and feedback from healthcare workers (qualitative)	Case notes Knowledge/skill test Interviews/focus groups
Quality of care – broader care	What is the quality of inpatient paediatric hospital care? Does the intervention improve healthcare workers’ broader care practices?	Mean quality of care score for target conditions (pneumonia, malaria, pre-term/small neonate) Proportion of admitted children discharged against medical advice Mean length of stay Healthcare worker motivation, satisfaction Structural and process determinants of care quality (medical supplies, hygiene, guidelines, clinical review meetings, record keeping, etc.)	Case notes Interviews

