### Data management and analysis

Clinical data will be collected from individual case notes by trained nurse data collectors. These data collectors will complete standardised Case Report Forms (CRF1) (see Additional file 2), which will be collated and returned to the project manager before being handed to the data manager. Trained data-entry clerks will double-enter the data into EpiData (EpiData Association, Odense, Denmark). The data manager will supervise the data entry and verification process, and will export the raw data file into.dta format for analysis using Stata v14 (StataCorp, College Station, TX, USA). All data will be de-identified before analysis to preserve confidentiality. The primary investigators will have full access to the data, and summary data will be made available for external validation purposes.

We will report characteristics of the individuals and clusters descriptively to illustrate potential imbalance between exposed and unexposed and allow for discussion of potential biases. We will illustrate the number of observations within each cluster by overlaying the summary numbers onto a stepped-wedge diagram. We will analyse effectiveness using intention-to-treat, according to the time hospitals were randomised to crossover. We will report any differences between intended crossover time and actual crossover time. We will adjust for the effect of calendar time, clustering, and other significant confounders using generalised linear mixed models (GLMM) or generalised estimating equations (GEE) [32, 44]. We will examine heterogeneity in effects between different hospitals using within-cluster comparisons of exposed and unexposed periods. This will contribute to better understanding of how various contextual factors influence effectiveness. We will conduct 6-monthly reviews of data for presentation to a supervisory committee, and to ensure that there is no evidence of significant unintended harm. Given the anticipated benefits and safety of this intervention, we do not have a formal data monitoring committee.

Equipment data will be collected by trained biomedical technicians during routine preventive maintenance visits. These technicians will complete standardised Case Report Forms (CRF2), and return them to the project manager. They will be entered and verified using the same procedures as for CRF1. We will report equipment outcome data descriptively, allowing for comparison between different hospitals.

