As expected, different hospitals have taken slightly different approaches to particular aspects of the intervention. For example, while hospital administrators have been open to alternative financing structures for oxygen, the actual implementation of this has been difficult in some hospitals due to administrative and governance requirements. We have been impressed with the ingenuity and problem-solving capacity of the participating hospitals, but informal feedback shows significant variability in the functioning of teams at different hospitals. This highlights the importance of measuring and reporting fidelity and other process indicators, in order to better understand this variability and how improved oxygen systems work in different contexts. Overall, the intervention appears to be achieving very high levels of fidelity, and early data shows large improvements in oxygen-related clinical behaviours (e.g. the use of pulse oximetry, administration of oxygen to hypoxaemic patients, etc.). Interim safety data suggests that the intervention is not causing harm and probably causing benefit, and we anticipate having adequate power to detect a meaningful difference by the end of data collection despite lower than expected admission numbers.

Oxygen therapy is a basic, life-saving therapy that is relevant for many paediatric and adult health conditions, but has limited global availability. Our study should provide quality evidence on the effectiveness of improved oxygen systems, and how to better implement and scale up oxygen systems in resource-limited settings. Our results will have important implications for policy-makers, hospital administrators, and child health organisations in Africa and globally. Our findings may have broader applicability to other healthcare interventions that are worthy of scale-up but are proving challenging to implement in the places that can benefit the most.

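### Oximetry-based severity is said to be needed for the primary analysis, but the intervention changes who is tested, so conditioning on recorded hypoxaemia can bias the case-fatality effect

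*Protocol article*

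**What the plan says.** The Intervention section of the protocol article gives the reason for handing out oximeters before the full package: "The early introduction of pulse oximetry will enable accurate classification of severity of illness and indication for oxygen (which is needed for primary analysis". The Study design section makes the same link, putting oximetry first "as hypoxaemia data is necessary for evaluation of the full intervention".

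Table 3 gives the oximetry support in each phase. Phase I has "One-hour basic pulse oximetry training for nurses and physicians when pulse oximeters are distributed". The clinical training material for the full package again lists "use of pulse oximetry and concentrators", and the health-information component supports adding SpO2 to monitoring charts. In phase II the coordination team also visits at least every 3 months.

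Table 4 lists as an oxygen-practice outcome "Proportion of admitted children who have pulse oximetry done correctly during admission", and beside it "Proportion of hypoxaemic children who correctly received oxygen therapy". The Discussion reports that "early data shows large improvements in oxygen-related clinical behaviours (e.g. the use of pulse oximetry" and other behaviours have been seen.

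The Abstract names pneumonia case fatality and inpatient neonatal mortality as primary. The footnote to Table 4 defines case fatality on the admitted population. On modelling, Data management and analysis says: "We will adjust for the effect of calendar time, clustering, and other significant confounders". Hypoxaemia is not named there. Clinical data come from case notes.

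**The concern.** Because data come from case notes, hypoxaemia is known only for children who were tested and whose result was written down. Phase II is built to change both steps. Recorded hypoxaemia is therefore measured after the hospital's randomised exposure and depends on it, so it is not a baseline severity variable that means the same in both phases.

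The article nevertheless says this classification is needed for the primary analysis, without saying how it enters. If it enters as a covariate, a stratifier or a restriction, the two phases are compared within groups whose membership changes at crossover. When detection rises, milder cases can move into the hypoxaemic group and undetected cases out of the apparently normal group. Case fatality can then fall in both groups although no child's outcome has changed. The open-ended adjustment rule does not guard against this, since the Background calls hypoxaemia an independent risk factor for death.

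The oxygen-treatment outcome in Table 4 has detected hypoxaemic children as its denominator, so it is exposed to the same shift.

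**Working it through.** The article gives no figure for this point, so there is none to reproduce. The check asks what analyses that condition on recorded hypoxaemia would show if the intervention had no effect on death.

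**Inputs from the article.** Hypoxaemia prevalence: 13% (severe pneumonia, systematic review), 29% (children under 5 at one tertiary hospital) and 49% (pneumonia at that hospital). Planned pneumonia effect: 6.1% to 4%, a 35% reduction.

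**Model 1, assumptions.** Hypoxaemic children split equally into obvious and less obvious. Case fatality is 3% (not hypoxaemic), 8% (less obvious) and 20% (obvious). Detection (obvious/less obvious) is 60%/20% unexposed and 95%/85% exposed. Untested children count as not hypoxaemic. The two periods are of equal size.

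Per 1,000 admissions at 29% prevalence:

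- True groups: 710 not hypoxaemic (21.3 deaths), 145 less obvious (11.6), 145 obvious (29.0). Total 61.9 deaths, 6.2%, in both periods.
- Unexposed, recorded hypoxaemic: 145 × 0.60 + 145 × 0.20 = 116; deaths 17.4 + 2.32 = 19.72, or 17.0%. The rest: 884 children, 42.18 deaths, 4.8%.
- Exposed, recorded hypoxaemic: 145 × 0.95 + 145 × 0.85 = 261; deaths 27.55 + 9.86 = 37.41, or 14.3%. The rest: 739 children, 24.49 deaths, 3.3%.
- Mantel-Haenszel odds ratio = Σ(exposed deaths × unexposed survivors / stratum total) ÷ Σ(unexposed deaths × exposed survivors / stratum total) = (37.41 × 96.28/377 + 24.49 × 841.82/1623) ÷ (19.72 × 223.59/377 + 42.18 × 714.51/1623) = 22.26/30.26 = 0.735.

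Odds ratios with exposed detection held at 95%/85%:

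| Prevalence | Unexposed 80%/60% | 60%/20% | 30%/5% |
|---|---|---|---|
| 13% | 0.931 | 0.825 | 0.751 |
| 29% | 0.892 | 0.735 | 0.622 |
| 49% | 0.873 | 0.694 | 0.561 |

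Overall case fatality in this model moves with prevalence, from 4.4% at 13% to 8.4% at 49%.

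**Model 2, to test direction.** Overall case fatality is fixed at the planned 6.1%. Assumptions: death risk ratio 4 for hypoxaemia and 3 for clinical severity; 30% of hypoxaemic and 10% of other children are severe; testing depends on severity. Risk ratios are phase II against phase I with no true effect; ranges are over the three prevalences.

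| Testing (severe, not severe), phase I → II | Recorded hypoxaemic only | Stratified, tested only | Stratified, untested = normal |
|---|---|---|---|
| Sicker first (0.6, 0.1) → (0.95, 0.85) | 0.68 | 0.68 | 0.76 to 0.61 |
| Milder selection (0.6, 0.3) → (0.95, 0.85) | 0.86 | 0.88 to 0.86 | 0.82 to 0.72 |
| High phase I uptake (0.9, 0.75) → (0.95, 0.9) | 0.97 | 0.97 | 0.96 to 0.93 |
| Non-selective 0.2 → 0.9 | 1.00 | 1.00 | 0.77 to 0.64 |
| Proportional rise (0.4, 0.1) → (0.96, 0.24) | 1.00 | 1.00 | 0.87 to 0.79 |
| Sickest missed (0.1, 0.4) → (0.9, 0.9) | 1.34 | 1.21 to 1.30 | 0.82 to 0.74 |
| Equal 0.9 → 0.9 | 1.00 | 1.00 | 1.00 |

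Without conditioning, all admissions give 6.1% against 6.1%, a risk ratio of 1.00, in every row.

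**Oxygen-treatment outcome.** Suppose oxygen reaches 40% of detected obvious and 10% of detected less obvious cases in both periods. Under Model 1 the recorded proportion is (0.60 × 0.40 + 0.20 × 0.10)/(0.60 + 0.20) = 32.5% unexposed and (0.95 × 0.40 + 0.85 × 0.10)/(0.95 + 0.85) = 25.8% exposed, with no change in care. If phase I instead misses the obvious cases (10%/40%, then 90%/90%), it moves from 0.08/0.50 = 16% to 0.45/1.80 = 25%. The direction again depends on who was tested.

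**The case against.** The strongest reply is that the article specifies no primary analysis that conditions on hypoxaemia. Both primary outcomes are rates among admitted patients, no mortality outcome in Table 4 is limited to hypoxaemic children, and hypoxaemia is not a named covariate. A full covariate list is normally left to the analysis plan. The parenthesis in the Intervention section could loosely refer to the oxygen-practice outcomes. This stands as far as the defined rates go: they are unbiased by this mechanism. It does not remove the statement that the classification is needed for the primary analysis, which nothing in the article reconciles with those definitions.

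A reader might infer that rising oximetry use by itself makes conditioned analyses show a benefit. It does not. Among recorded-hypoxaemic or tested children, the bias is nil when testing is non-selective or rises in proportion, and it runs towards harm when phase I misses the sickest. A bias towards benefit needs sicker-first testing in phase I, or untested children coded as normal. The article states neither.

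A reader might also take the Discussion as proof of a jump at crossover. It gives no figures and does not separate phase I from phase II. Nine of the 12 hospitals had no oximeter at baseline (Table 2), so part of the rise may have come with phase I distribution, and a rise completed before the phase I data began would not bias the comparison. The concern rests on the design of phase II in Tables 3 and 4, not on that sentence.

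The magnitudes rest on assumed detection and fatality rates, and the two higher prevalences come from a tertiary hospital whereas the trial hospitals are secondary-level.

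**Conclusion.** The point holds in a limited form. The article ties its primary analysis to a variable that its own intervention is designed to alter. Using that variable for adjustment, stratification or restriction can bias the case-fatality effect. With untested children counted as non-hypoxaemic, every scenario in which uptake rose gave a spurious benefit, with odds ratios of 0.93 to 0.56 in the first model. Under sicker-first testing the spurious risk ratio among recorded-hypoxaemic children is 0.68, close to the planned 35% reduction; with high phase I uptake it is only 0.97. These sizes are illustrations, because the article reports no testing rates by phase.

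The documents do not support saying that the primary result is, or will be, biased. Case fatality on all admissions is unaffected. The mechanism applies equally to neonates, but no size was computed for them.

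**What to change.** 1. In the Intervention section, remove or correct the parenthesis about the primary analysis.
2. In Data management and analysis, state that the primary case-fatality models include all eligible admissions and do not restrict to, stratify by or adjust for recorded SpO2 or hypoxaemia. Adjustment may use characteristics that oximetry practice cannot change, such as age, sex, hospital and calendar period.
3. Label any mortality result conditioned on hypoxaemia as secondary, with sensitivity analyses for how untested patients are handled.
4. Keep the Table 4 oxygen-treatment outcome, report it beside oximetry coverage by hospital and period, and note that its denominator can shift at crossover. Replacing it with hypoxaemic-and-treated per 100 admissions is not advised as the main measure: that figure rises with testing alone and mixes detection with treatment.

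This is a change of wording and reporting with no new data. The cost is one prognostic covariate in the primary model and slightly less precision.

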Procurement, installation, and maintenance structures procurement advice and support installation support maintenance procedures financing procedures	To enable reliable, continuous access to oxygen for all children and neonates To build hospital team capacity to maintain and scale up oxygen systems. To strengthen hospital’s technical capacity to maintain and repair equipment To make oxygen therapy affordable for both patients and hospitals	Uniform equipment procurement led by coordination team, in collaboration with participating hospitals Equipment installation led by central technical team in collaboration with participating hospitals, and delivered in partnership with technicians from participating hospitals Equipment procedures and forms developed by coordination team in collaboration with participating hospitals. A comprehensive maintenance plan must involve the provider, installer, engineer, local technician, and local clinical staff (including timely access to technical support) Local challenges identified during participatory planning, and addressed by local hospital teams Cost-analysis conducted by coordination team with hospital-level data, and recommendations made for action by hospital administrators
Infrastructure support improved power supply (e.g. solar power)	To ensure reliable, continuous access to oxygen for all children and neonates. To make it easy to maintain oxygen equipment in good function	Improved power system using solar capture and/or battery storage and/or generator back-up. The exact configuration has not been pre-specified, but will be based on hospital-level power evaluations, and recommendations from expert engineers/technicians (including mathematical modelling). Power system should be effective, efficient, user-friendly, and able to be maintained by local technicians. Other potential needs may include: secure storage areas, enhanced security arrangements, workspace modification, etc.
Strengthening health information systems clinical documentation medical records	To strengthen broader care processes. To strengthen managerial support for oxygen therapy.	Support nursing and medical staff to improve documentation (e.g. adapt monitoring charts to include peripheral capillary oxygen saturation (SpO_2_)) Support medical records staff with record keeping and reporting (e.g. basic electronic health reporting system on computer)

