### Clinical outcomes

We will collect data on clinical outcomes from case notes to evaluate clinical effectiveness and to enable exploration of variability of effect between hospitals. The primary clinical outcome will be in-hospital case fatality rates for the target population. Secondary clinical outcomes will include a range of quality of care measures relating to oxygen therapy, and supportive care. We will assess quality of care based on key clinical activities at various stages of care (assessment, diagnosis/classification, management, monitoring) based on WHO guidelines for the hospital care for children [35]. This approach is similar to the recently described Paediatric Admission Quality of Care (PAQC) score [36].

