### Sample size

We made sample size and power estimates using the Stata menu-driven programme *steppedwedge*, which is based on the Hussey and Hughes’ method for calculating sample size for a stepped-wedge trial [44, 45]. We based our assumptions on admission, prevalence, and case-fatality rate data from our needs-analysis, and informed by correlation estimates from previous studies [46]. We estimated that we would enrol approximately 16,770 children and 7670 neonates (1290 preterm) over the course of the study. Based on an alpha of 5%, we calculated that we would have approximately 80% power to detect a 35% reduction in pneumonia case fatality rate (6.1% to 4%), and 90% power to detect a 20% reduction in neonatal case fatality rate (8.2% to 6.6%). We would have greater than 90% power to detect 10% change in quality of care scores.

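### Case-note quality-of-care outcomes may rise with exposure because recording improves, since phase II also supports documentation, and the planned model cannot separate this from better care

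*Protocol article*

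**What the plan says.** All places are in the protocol article, under Methods/design unless stated.

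- **Outcomes.** Table 4 lists "Mean quality of care score for oxygen therapy" and "Mean quality of care score for target conditions (pneumonia, malaria, pre-term/small neonate", together with proportions for oximetry done, oxygen given to hypoxaemic children, and "Proportion of children receiving oxygen who had a documented clinical indication for oxygen". Case notes are a source for both rows. The other sources in those rows are knowledge/skill tests and interviews or focus groups.
- **Construction of the score.** Clinical outcomes: "We will assess quality of care based on key clinical activities at various stages of care".
- **Data capture.** Data management and analysis: "Clinical data will be collected from individual case notes by trained nurse data collectors".
- **Intervention.** The Intervention section includes among the phase II components "6) strengthening disease surveillance and health information systems, and (7) strengthening quality improvement processes". Table 3 describes the health-information component in part as: "Support nursing and medical staff to improve documentation (e.g. adapt monitoring charts to include peripheral capillary oxygen saturation".
- **Baseline.** Table 2 rates clinical records as fair at all 12 hospitals.
- **Analysis.** Effectiveness is analysed by randomised crossover time, with adjustment for calendar time, clustering and confounders.
- **Power.** Sample size: "greater than 90% power to detect 10% change in quality of care scores".

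**The concern.** A score abstracted from notes reflects two things: whether a task was done, and whether it was written down. Phase II acts on both. If staff record more of what they already do, the score can rise while care stays the same.

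A stepped-wedge analysis protects against secular trends and fixed differences between hospitals. It does not protect against a change in the measuring instrument that is itself part of the exposure.

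Table 4 asks whether the intervention improves staff practice, both for oxygen and for care more broadly. The Implementation outcomes section asks whether the intended mechanisms were affected. If better recording is reported as better practice, both questions could be answered wrongly. The Discussion already describes early data as showing large gains in oxygen-related behaviour, although it does not say which data these are.

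**Working it through.** **1. The plan's own figure.** The article gives over 90% power for a 10% change in quality scores. It does not give the SD, intracluster correlation (ICC), baseline score or number scored, and it does not say whether 10% is absolute or relative. The figure cannot be reproduced exactly, but its plausibility can be checked with the Hussey–Hughes variance the article relies on:

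Var = Iσ²(σ² + Tτ²) / [(IU − W)σ² + (U² + ITU − TW − IV)τ²]

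- Design: I = 12 hospitals and T = 6 periods, with three hospitals crossing over at each of steps 2 to 5.
- U = 3 × (5+4+3+2) = 42.
- W = 0² + 3² + 6² + 9² + 12² + 12² = 414.
- V = 3 × (25+16+9+4) = 162.
- IU − W = 504 − 414 = 90.
- U² + ITU − TW − IV = 1764 + 3024 − 2484 − 1944 = 360.
- σ² = SD²/n, where n is the number per hospital-period, and τ² = SD² × ICC/(1 − ICC).
- Assumed, because not stated: within-hospital SD 20–30 points, ICC 0.01–0.20, equal cells (N/72), two-sided 5%.

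Example for neonates: n = 7670/72 = 106.5. With SD 30 and ICC 0.20, σ² = 900/106.5 = 8.45 and τ² = 900 × 0.25 = 225. Then Var = 12 × 8.45 × (8.45 + 1350) / (90 × 8.45 + 360 × 225) = 1.69, so SE = 1.30.

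| Sample | N | SE, points | Power for 10 points |
|---|---|---|---|
| Children | 16,770 | 0.58–0.88 | about 100% |
| Neonates | 7670 | 0.84–1.30 | about 100% |
| Preterm | 1290 | 1.90–3.14 | 89–100% |

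The stated power is plausible. These SEs are optimistic: hospital sizes in Table 2 are very unequal (185 to 3431 annual admissions), the Discussion reports fewer admissions than expected, and condition-specific scores use only part of each sample.

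**2. What better recording alone could do.** Let p be the share of tasks done, unchanged by exposure, and r the share of done tasks that are recorded. If an unrecorded task scores zero:

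score = p × r; absolute artefact = p × (r₁ − r₀); relative artefact = r₁/r₀ − 1.

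- p = 0.60, r from 0.60 to 0.80: score 0.36 to 0.48, a rise of 12 points. This uses the largest recording gain in the range considered.
- p = 0.50, gain 0.10: 5 points. p = 0.70, gain 0.20: 14 points. The range is therefore 5–14 points.
- A 10-point recording gain gives a relative rise of 16.7% (from 60%), 14.3% (from 70%) or 12.5% (from 80%), whatever p is.
- Read as absolute, a rise of about 10 points needs a larger gain. With p = 0.70, a 15-point gain gives 0.70 × 0.15 = 10.5 points.

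The values of p and r, their independence, and the zero-scoring rule are all assumptions. None is in the article.

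**3. Would such a shift be detected as an effect?** Five points is at least 5/1.30 = 3.8 SEs in the full child and neonatal samples under the assumptions in step 1. With 1290 preterm neonates and the largest SE it is 5/3.14 = 1.6 SEs. In the larger samples the test would therefore not screen out a recording-only shift of this size.

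**4. Can the other sources separate the two?** Knowledge/skill tests measure what staff know. Interviews and focus groups measure attitudes, motivation and structure. Neither shows whether a task was done for a given patient. The article describes no check of notes against care given.

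**The case against.** The strongest reply is that this is inherent in any case-note audit, that better documentation is an intended effect, and that the outcomes are secondary. All three are true and limit the severity. They do not justify reading the score as care delivered.

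Several stronger readings are tempting but unsupported:

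- *A reader might infer an abrupt change in the notes at crossover.* The article places documentation support in phase II but does not date the chart changes. Oximeters and basic oximetry training arrive in phase I at all hospitals, so some SpO₂ recording may improve earlier. Supervision visits at least every 3 months suggest gradual change. The link with exposure remains, but a sharp step is not shown.
- *A reader might take 5–14 points as an estimate of bias.* It is an illustration. The scoring rule is not stated, and the case report form is in an additional file that is not shown.
- *A reader might count the documented-indication proportion as mismeasured.* It is a recording measure by definition, so better recording is part of what it measures.
- *A reader might treat all record-keeping support as changing case notes.* Part of it is directed at medical records staff and reporting, which is closer to administrative records.
- *A reader might say nothing in the plan bears on the problem.* Table 4 includes record keeping as a determinant of quality, and qualitative data will explore reasons for observed effects. These help interpretation without separating recording from care patient by patient.

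An analysis plan, not shown, might hold further models. The point does not rest on their absence. It rests on an intervention component and a data source that the article itself states and that overlap.

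**Conclusion.** The concern holds for the secondary quality-of-care scores and for the oximetry and oxygen-practice proportions taken from notes. Recording may improve with exposure, records have room to improve, and the planned adjustment cannot separate that from better care. Followed as written, the plan could report better recording as better practice.

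The direction is clear, since more complete notes raise the score, but the size is unknown. The 5–14 points depend wholly on the assumed performance, recording gains and zero-scoring rule.

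A reader might extend the point to the mortality result or to the whole mechanism analysis. The article does not support that. In-hospital death depends much less on how fully care is charted, although diagnosis-defined denominators also come from notes, and mechanisms are examined with mixed data. This is a change that should be made to what the quality outcomes are allowed to conclude. It does not invalidate the trial.

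**What to change.** 1. Add a recording-completeness outcome built from items already abstracted that are not scored as care, for example age and admission and discharge dates. Analyse it with the same exposure and calendar-time model as the quality scores. Leave out weight and temperature: these are care activities that the clinical training may itself improve.
2. State that quality results from case notes are reported as *documented care*, and that improved care practice will not be claimed from the score alone, particularly if completeness rises with exposure.
3. Show score items on adapted charts separately, as a descriptive sensitivity analysis only. The remaining items are also exposed to general documentation support, so they are not a clean comparison.

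**Cost.** One extra model, some wording, and a more cautious quality-of-care conclusion. Data collection is under way, so the control items must be confirmed as present on the case report form. If they are already nearly complete before crossover, the completeness outcome will have little sensitivity, and a flat result should not be taken as proof that recording of care was stable.
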